## Abstract

**Introduction:** Optimizing patient safety and quality improvement is increasingly important in surgery. Benchmarks and clinical quality registries are being developed to assess the best achievable results for several surgical procedures and reduce unwarranted variation between different centers. However, there is no clinical database from international centers for establishing standardized reference values of patients undergoing surgery for mesial temporal lobe epilepsy.

**Design:** The Enhancing Safety in Epilepsy Surgery (EASINESS) study is a retrospectively conducted, multicenter, open registry. All patients undergoing mesial temporal lobe epilepsy surgery in participating centers between January 2015 and December 2019 are included in this study. The patient characteristics, preoperative diagnostic tools, surgical data, postoperative complications, and long-term seizure outcomes are recorded.

**Outcomes:** The collected data will be used for establishing standardized reference values (“benchmarks”) for this type of surgical procedure. The primary endpoints include seizure outcomes according to the International League Against Epilepsy (ILAE) classification and defined postoperative complications.

**Discussion:** The EASINESS will define robust and standardized outcome references after amygdalohippocampectomy for temporal lobe epilepsy. After the successful definition of benchmarks from an international cohort of renowned centers, these data will serve as reference values for the evaluation of novel surgical techniques and comparisons among centers for future clinical trials.

**Clinical trial registration:** This study is indexed at clinicaltrials.gov (NT 04952298).

## Introduction

Surgeons strive for the best possible outcome from their operations with the greatest possible chance for recovery and cure of the patients. To optimize the outcome, the continuous monitoring and measurement of key elements of surgical procedures are indispensable. To this end, the number of clinical registries has increased in recent years (1). To evaluate surgical quality, recent initiatives aim to assess the best achievable results for several surgical procedures and reduce unwarranted variation between different centers (2–4). A standardized methodology to describe optimal outcomes in neurosurgery is lacking. The most appealing concept in surgery is a combination of various clinical indicators with risk stratification and a focus on treatment efficacy and adverse events. This offers a more reliable analysis than single-outcome indicators, such as survival or readmission rate (5–10). Nevertheless, an establishment of clinical databases from international centers with an accurate collection of demographic, management, and outcome data for respective surgical procedures is needed. The importance of establishing benchmarks has been demonstrated for various surgical procedures in general and visceral surgery (11–15). As yet, there is very little published about acceptable neurosurgical benchmarks. A benchmark establishes standardized reference values which represent the acceptable common outcome of high-volume centers and can be used for comparison and improvement. Best results are obtained from patients at the lowest risk (10). Therefore, the cohort must be divided into low-risk and high-risk patients according to the defined benchmark criteria that predict a potentially worse postoperative outcome.

The aim of this international multicenter register [Enhancing Safety in Epilepsy Surgery (EASINESS)] is to define robust and standardized outcome references after amygdalohippocampectomy and anteromedial temporal lobectomy for temporal lobe epilepsy. After the successful determination of benchmarks from an international cohort of renowned centers, these data will serve as reference values for the evaluation of novel surgical techniques and comparisons among centers for future clinical trials. They will provide feedback to participating centers to enable deficiencies in care to be addressed, thereby enabling quality improvement. This registry will demonstrate the feasibility and utility of risk-stratified benchmarked data for neurosurgical practice.

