## Materials and Methods

### Study Design

The EASINESS is a retrospectively conducted, multicenter, open registry. The study is a procedure-specific registry, initiated by the Department of Neurosurgery, University Medical Center Hamburg-Eppendorf, Germany. The selected members of participating neurosurgical or epilepsy centers will be invited to form a Steering Committee, which will be responsible for the scientific goals and guarantee the reliability of the data analysis. Neurosurgical, neurological, and epilepsy units from all countries are invited to join the trial and to recruit patients if the center- and patient-specific inclusion criteria are met.

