### Study Setting and Type of Participants

All patients undergoing mesial temporal lobe epilepsy surgery between January 1, 2015 and December 31, 2019 are included in the study. The following surgical procedures are included: selective amygdalohippocampectomy including anterior parahippocampal gyrus/entorhinal cortex, anteromedial temporal lobe resection including amygdalohippocampectomy with approximately anterior third of the temporal neocortex, amygdala, uncus, hippocampus, anterior parahippocampal gyrus/entorhinal cortex, and anterior temporal lobe resection with two-thirds of the temporal neocortex, amygdala, uncus, hippocampus, and anterior parahippocampal gyrus/entorhinal cortex (16, 17). Patients who went through deep brain stimulation, vagus nerve stimulation, neocortical temporal resection only, or a recurrent resection are not included in this study.

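### The target procedure is named in three different ways, and the stated cut-off rule does not separate the three eligible resections

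*Protocol article*

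**What the plan says.** The protocol article describes its target in several places.

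- Abstract, Discussion paragraph: the registry "will define robust and standardized outcome references after amygdalohippocampectomy for temporal lobe epilepsy".
- Introduction, aim: "to define robust and standardized outcome references after amygdalohippocampectomy and anteromedial temporal lobectomy for temporal lobe epilepsy".
- Study Setting and Type of Participants: three operations are eligible. The list opens with "The following surgical procedures are included: selective amygdalohippocampectomy including anterior parahippocampal gyrus/entorhinal cortex", continues with "anteromedial temporal lobe resection including amygdalohippocampectomy with approximately anterior third of the temporal neocortex", and ends with "anterior temporal lobe resection with two-thirds of the temporal neocortex, amygdala, uncus, hippocampus" and the anterior parahippocampal structures. Table 1 repeats the same three.
- Study Design: "The study is a procedure-specific registry".
- The Abstract's Design paragraph and the article's Discussion use broader names (mesial temporal, or simply temporal, lobe epilepsy surgery) that cover all three.

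The Statistics section stratifies patients into low and high preoperative risk on the basis of comorbidities. It then sets the cut-off for each indicator at the 75th percentile across centres. Procedure type appears in neither step. The Case Report Form section shows that procedure type is recorded.

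**The concern.** The sentences that say what is being benchmarked do not agree with each other or with eligibility. The resection that takes two-thirds of the temporal neocortex is enrolled, but neither the Abstract's target sentence nor the aim mentions it.

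This matters because of how the values will be used: to compare centres, to feed back deficiencies in care, and to judge new techniques. The Introduction says the cohort must be divided by criteria that predict a worse outcome, yet the Statistics section carries this out through comorbidities only. A comorbidity split does not adjust for extent of resection. If the risk of a new deficit or the chance of seizure freedom depends on extent, a centre's position against the cut-off reflects which operations it does as well as how well it does them. A reader could not tell the two apart from the overall value.

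**Working it through.** **1. The texts side by side**

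| Place | Procedures named | Two-thirds resection named? |
|---|---|---|
| Abstract, Discussion paragraph | 1 | No |
| Introduction, aim | 2 | No |
| Study Setting; Table 1 | 3 | Yes |

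Could amygdalohippocampectomy be an umbrella term? By the structures listed, all three operations remove amygdala and hippocampus, so the Abstract's sentence can be read that way. The aim cannot easily be: it lists anteromedial lobectomy separately, as a second item. On that usage the third operation lies outside the stated aim.

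**2. What the cut-off rule does with procedure type**

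The rule gives a cut-off per indicator, draws on all centres, and names one stratifier, comorbidity-based risk. The regression sentence in the same section is general and is not tied to the cut-off or to procedure. Combining the three resections is therefore the natural reading, although the text does not say so.

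**3. How procedure mix enters a centre's value**

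The article states no rate, sample size or procedure mix, so there is no figure of its own to reproduce. Everything below rests on assumed inputs.

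With rate p_S after the selective operation, p_L after the two-thirds resection, and a share m of large resections, a centre's expected rate is (1 − m)·p_S + m·p_L. Two centres of equal quality with shares m1 and m2 differ by (m2 − m1)·(p_L − p_S).

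For p_S = 5% and p_L = 10%:

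- m = 0.10: 0.9 × 5 + 0.1 × 10 = 5.5%
- m = 0.90: 0.1 × 5 + 0.9 × 10 = 9.5%
- difference 4.0 points, ratio 9.5 / 5.5 = 1.73

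With the same two shares (m2 − m1 = 0.8) and other assumed differences in rates:

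| p_L − p_S (points) | Difference between the centres (points) |
|---|---|
| 0 | 0.8 × 0 = 0 |
| 4 | 0.8 × 4 = 3.2 |
| 5 | 0.8 × 5 = 4.0 |
| 10 | 0.8 × 10 = 8.0 |

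Shares of 10% and 90% are extreme; closer shares shrink the difference in proportion.

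**4. Effect on the cut-off itself**

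The simulation assumed 20 centres of equal quality with 100 patients each, and 4,000 replicates. For a complication (yes/no), the cut-off was taken as the 75th percentile of the centre rates. The mix of three procedures was either the same in all centres, varied or very varied. Procedure-specific cut-offs also used 100 patients per centre, which is generous. The last column is the chance that a centre doing only one of the procedures, with 100 patients, exceeds the overall cut-off.

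| Assumed rates, smallest to largest resection | Overall cut-off | Procedure-specific cut-offs | Chance of exceeding the overall cut-off |
|---|---|---|---|
| 10 / 10 / 10% | 11.8% | 11.8 / 11.8 / 11.8% | 0.30 / 0.30 / 0.30 |
| 8 / 10 / 12% | 11.8–12.0% | 9.7 / 11.8 / 14.0% | 0.10 / 0.30 / 0.55 |
| 5 / 10 / 15% | 11.8–12.6% | 6.3 / 11.8 / 17.2% | 0.00 / 0.20–0.30 / 0.75–0.84 |

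With equal rates, combining the procedures does no harm, and 0.30 is the exceedance expected from chance alone. With a spread of 4 to 10 points between the extreme procedures, the overall cut-off lies about 2 to 6 points from the values specific to those two procedures (for example 11.8 − 9.7 = 2.1, and 12.6 − 6.3 = 6.3). The seizure outcome was not simulated. The formula in step 3 applies to any proportion, but the article gives no rates for that outcome either.

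**The case against.** The strongest reply has four parts.

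- **Nothing operational is unclear.** Study Setting and Table 1 agree, so no site would enrol the wrong patient because of the shorter wording elsewhere. This stands, and it means that aligning the names would on its own be an editorial matter.
- **The name can be read broadly.** A reader might infer that the benchmark fails to describe the operation it is named for. The document does not support that: amygdala and hippocampus are removed in all three resections, and the Abstract and Discussion also use names that cover all of them. A procedure-specific registry can equally mean one limited to this family of operations.
- **Pooling is inferred.** A reader might take it as settled that only one combined value will be reported. The article never says so, it refers its method to earlier benchmarking studies, and a fuller plan may add tables by procedure. That limits the point to the rule as written. It does not remove it, because the article does state its stratifier and its cut-off rule, and procedure type is in neither.
- **A combined benchmark is defensible.** Extent of resection is partly a centre's choice, and conditioning on it could hide the unwarranted variation that the registry wants to expose. Splitting by procedure within risk groups also thins the data; the volume threshold of 30 per year counts all seizure-specific resections, not only mesial temporal ones. This stands as a reason to keep the overall cut-off. It is no reason to withhold the values by procedure beside it.

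**Conclusion.** The inconsistency in naming is real and in the current text: one, two or three procedures depending on the section, with the largest eligible resection outside the stated aim. The cut-off rule, as written, divides the cohort only by comorbidity-based risk and does not separate resection types. A centre's value may therefore partly reflect its procedure mix.

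The size cannot be determined from the article, which gives neither rates nor mixes. It is nil if rates are equal across procedures or if all centres have the same mix. The 1.7-fold difference between two centres and the 2 to 6 point gap in cut-offs are illustrations on assumed inputs, not estimates for this registry.

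A reader might also infer that a new technique should be compared only with the value for a matching procedure. The documents do not support that restriction: a new technique need not correspond to any of the three resections, and a benchmark for the whole eligible group is a legitimate choice.

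**What to change.** 1. Name the same three resections in the Abstract's Discussion paragraph and in the aim as in Study Setting and Table 1.
2. Keep the overall cut-off as the benchmark.
3. For each indicator, also report the value by procedure type, which the case report form already records. Where a procedure has too few centres for a percentile cut-off, give its overall rate with a 95% interval, and set that minimum number of centres before the values are tabulated.

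This forces no choice between combined and separate values, and it shows whether procedure mix drives differences between centres. The cost is aligned wording and one further table from data already collected. The downside is wider uncertainty in the procedure-specific values, which the table should make visible.

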## Materials and Methods

### Study Design

The EASINESS is a retrospectively conducted, multicenter, open registry. The study is a procedure-specific registry, initiated by the Department of Neurosurgery, University Medical Center Hamburg-Eppendorf, Germany. The selected members of participating neurosurgical or epilepsy centers will be invited to form a Steering Committee, which will be responsible for the scientific goals and guarantee the reliability of the data analysis. Neurosurgical, neurological, and epilepsy units from all countries are invited to join the trial and to recruit patients if the center- and patient-specific inclusion criteria are met.

### Study Setting and Type of Participants

All patients undergoing mesial temporal lobe epilepsy surgery between January 1, 2015 and December 31, 2019 are included in the study. The following surgical procedures are included: selective amygdalohippocampectomy including anterior parahippocampal gyrus/entorhinal cortex, anteromedial temporal lobe resection including amygdalohippocampectomy with approximately anterior third of the temporal neocortex, amygdala, uncus, hippocampus, anterior parahippocampal gyrus/entorhinal cortex, and anterior temporal lobe resection with two-thirds of the temporal neocortex, amygdala, uncus, hippocampus, and anterior parahippocampal gyrus/entorhinal cortex (16, 17). Patients who went through deep brain stimulation, vagus nerve stimulation, neocortical temporal resection only, or a recurrent resection are not included in this study.

### Center-Specific Inclusion Criteria

The participating centers need to perform 30 or more seizure-specific resections as an average per year during the 5-year study period. This threshold is based on the recommendations of the German Society for Epileptology and the Austrian, German, and Swiss working group on presurgical epilepsy diagnosis and operative epilepsy treatment for certification as an epilepsy center performing epilepsy surgery (18, 19). International centers may be accepted on a case-by-case basis if they meet the alternative local guidelines for epilepsy center definition. The implantation of vagus nerve stimulators was not counted toward the number of seizure-specific procedures (Table 1).

**Table 1 T1:** Inclusion and exclusion criteria for centers and patients to participate in the Enhancing Safety in Epilepsy Surgery (EASINESS) registry.

**Inclusion criteria**	**Exclusion criteria**
Center-specific:	
1. Centers with ≥30 seizure-specific resections (excluding vagus nerve stimulation) as an average per year during the study period	
Patient-specific:	
1. Patients who went through mesial temporal lobe epilepsy surgery, including: a. Selective Amygdalohippocempectomy including anterior parahippocampal gyrus / entorhinal cortex b. Anteromedial temporal lobe resection including amygdalohippocampectomy c. Anterior temporal lobe resection	1. Patients who went through neocortical temporal resection only 2. Patients who went through recurrent resection

### Informed Consent

Written informed consent is not required in this retrospective study since all patient data are processed anonymously. The study was approved by the Institutional Ethics Committee centrally at University Medical Center Hamburg-Eppendorf and local governance approval was obtained by each site as necessary. The patients' data were extracted and analyzed following the declaration of Helsinki.

### Data Collection

According to a standardized template for mesial temporal lobe epilepsy surgery, patient-specific data, surgical details, postoperative complications, and long-term seizure outcome including neuropsychological assessment will be recorded. The data acquisition will be electronic-based (case report form, CRF), and patient-specific data will be de-identified by the study center. The data will then be transferred into an electronic database and further analyses made at the Department of Neurosurgery, University Medical Center Hamburg-Eppendorf.

### Case Report Form

The specially designed and developed Case Report Form (CRF) consists of four parts (Figure 1).

*Patient characteristics:* The first part of the CRF covers preoperative characteristics including patient demographic and baseline characteristics (sex, age, body mass index, educational status, neurological status), comorbidities (diabetes, congestive heart failure, coagulopathy, and COPD), and the American Society of Anesthesiologists (ASA) Physical Status Classification. In addition, seizure-specific features such as a history of neonatal seizure, febrile seizure, encephalitis or meningitis, age at epilepsy onset, type of seizure, average monthly frequency of seizures, and a number of anticonvulsive drugs at the time of surgery are registered. Furthermore, presurgical diagnostic tools (e.g., invasive monitoring, PET, SPECT, MEG) and possible lesions in MRI will be documented.*Surgical data:* This part covers all aspects of mesial temporal lobe epilepsy surgery. Here, type of procedure, intraoperative navigation, resection of the dominant or non-dominant hemisphere, side of resection, and the operating duration are registered.*Postoperative complications:* The fourth part addresses all questions of the outcome until discharge after index surgery. Postoperative complications such as stroke, surgical site infection, meningitis, reoperation, new neurological deficits, and in-hospital mortality will be recorded. In addition, the histological finding of the resected lesion is registered.*Follow-up:* Long-term clinical and seizure outcome after 12 months and an optional later time will be recorded. Here, long-term complications such as reoperation, temporalis muscle atrophy, and neurological deficits are registered. To analyze the seizure-specific outcome after surgery, the International League Against Epilepsy (ILAE) outcome scale, neuropsychological assessment (verbal and figural memory, attention), and the number of antiseizure medications will be documented.

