### Statistics

The endpoints will be evaluated using descriptive statistics, and the key figures of the distributions will be presented in tables. Statistical analyses will be made as described in previous studies which established the concept of benchmarking for other surgical procedures (10, 11, 15). Hereby, the cohort is stratified into patients with a low-preoperative and high-preoperative risk profile according to comorbidities which are proven to negatively impact the postoperative course. Afterward, the benchmark cut-off for each outcome indicator is set at the 75th percentile of the median of all centers (10). Depending on the composition of the data, χ2, Mann-Whitney U, and *t*-tests, or Pearson or Spearman correlation coefficients, will be conducted. The relationships between multiple independent variables on the dependent variable(s) will be tested using multivariate regression analysis.

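### The early-complications part of the CRF closes at discharge rather than on a fixed day, so recorded infection and death rates may depend on each centre's length of stay

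*Protocol article*

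**What the plan says.** The Abstract gives two primary endpoints and no time window for the second: "The primary endpoints include seizure outcomes according to the International League Against Epilepsy (ILAE) classification and defined postoperative complications".

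The only windows are in the Case Report Form section.

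- **Early part.** "The fourth part addresses all questions of the outcome until discharge after index surgery". (It is listed third of four; the numbering slip has no bearing here.) Its contents are: "Postoperative complications such as stroke, surgical site infection, meningitis, reoperation, new neurological deficits, and in-hospital mortality will be recorded".
- **Follow-up part.** "Long-term clinical and seizure outcome after 12 months and an optional later time will be recorded". On complications it adds: "Here, long-term complications such as reoperation, temporalis muscle atrophy, and neurological deficits are registered".

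The Statistics section turns the endpoints into centre-level reference values: "the benchmark cut-off for each outcome indicator is set at the 75th percentile of the median of all centers". The Introduction and Discussion say these values are for comparing centres and judging new techniques.

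**The concern.** Discharge is a centre-dependent end point for an observation window. Study Design invites units from all countries, and Center-Specific Inclusion Criteria admits some under alternative local guidelines, so a common discharge practice cannot be assumed. If some infections or deaths occur after patients go home, a centre that discharges earlier records fewer of them at the same true risk and looks safer.

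The benchmark is built from these centre values, so the distortion can carry into the reference level. A later study that counts complications over 30 days could then look worse against it for reasons unrelated to quality.

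This is a data-collection choice, which is why it matters now. If event dates and post-discharge events are not collected, no analysis plan can recover a fixed-window rate afterwards. The items the article lists for the CRF do not name length of stay or discharge date, so it shows no means of adjusting for window length. The stated limitation (retrospective, non-randomised) does not cover this.

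**Working it through.** **Step 1: compare the two CRF parts, using the items the article names.**

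| Event | Part ending at discharge | 12-month follow-up |
|---|---|---|
| Reoperation | named | named |
| Neurological deficit | named (new) | named |
| Surgical site infection | named | not named |
| Meningitis | named | not named |
| Stroke | named | not named |
| Death | in-hospital only | not named |
| Temporalis muscle atrophy | not named | named |

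Two of the six early events are carried forward and four are not. Both lists are introduced as examples.

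**Step 2: is there a figure in the plan to reproduce?** No. The article states no complication rate, onset time, length of stay or sample size. What follows is illustration on assumed values.

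**Step 3: share of events recorded by discharge.** Assume every centre has the same true risk and onset is exponential with median m days. Let L be the length of stay in days.

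*Model A, no upper limit on onset:* captured share = 1 − 0.5^(L/m).

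*Model B, onset limited to the first 30 days:* captured share = [1 − 0.5^(L/m)] / [1 − 0.5^(30/m)], where m is the median before truncation.

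| Model | m (days) | L = 3 | L = 10 | Ratio |
|---|---|---|---|---|
| A | 8 | 0.229 | 0.580 | 2.5 |
| A | 12 | 0.159 | 0.439 | 2.8 |
| A | 16 | 0.122 | 0.352 | 2.9 |
| B | 7 | 0.271 | 0.662 | 2.4 |
| B | 14 | 0.178 | 0.505 | 2.8 |

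Example, model A with m = 12: 1 − 0.5^(3/12) = 0.159, 1 − 0.5^(10/12) = 0.439, and 0.439/0.159 = 2.8.

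**Step 4: as recorded rates.** With an assumed true 30-day risk of 4% under model B, a 3-day stay records 4% × 0.271 = 1.1% (m = 7) or 4% × 0.178 = 0.7% (m = 14). A 10-day stay records 4% × 0.662 = 2.6% or 4% × 0.505 = 2.0%. The assumed risk cancels from the ratio, so 2% or 6% gives the same ratios.

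**Step 5: how far the chosen stays drive the result.** With stays of 5 and 7 days under model B, the captured shares are 0.412 and 0.527 (m = 7), a ratio of 1.3, and 0.283 and 0.379 (m = 14), also 1.3. The direction stays the same, but the size depends on how much discharge practice really varies.

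**The case against.** A reader might infer that complications are counted only until discharge, and that infections and deaths after discharge are never counted. The article does not support either statement.

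- The follow-up part registers long-term complications and names reoperation and neurological deficits again. A late infection needing surgery could appear there as a reoperation, and a late stroke as a deficit.
- The follow-up list is illustrative and sits under a wider clinical outcome. Figure 1, the full CRF and the standardised template are not shown. A 12-month form would ordinarily have to account for patients who died, though the article does not say how. The text supports only that these events are not named.
- The Abstract does not say which CRF part supplies the primary complication endpoint. The shared term makes the early part the natural reading, but it remains an inference.
- The arithmetic compares two hypothetical centres and does not estimate the effect on the benchmark itself. A cut-off taken near the upper end of centre values may be set more by longer-stay centres, so how far it would be understated is not shown.
- In a retrospective review of 2015–2019 operations, in-hospital events are the most evenly documented. Post-discharge events depend on referral and follow-up patterns, so a fixed window may bring in another centre-dependent bias.

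The first four points stand and limit the wording and the size claimed. They do not remove the stated rule: the early part ends at discharge, its mortality is in-hospital, and no common early window appears anywhere in the article. The fifth point is a real cost, but it can be managed by reporting both rates and the completeness of follow-up.

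**Conclusion.** The concern holds in a limited form. The article fixes discharge as the end of the early-complications part and leaves infection, meningitis, stroke and death unnamed at 12 months. If the primary complication endpoint is drawn from that part, and if a material share of these events occurs after discharge, recorded rates will vary with discharge practice at equal true risk. Short-stay centres will then look better than they are.

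The size cannot be derived from the article. The 2.4- to 2.9-fold contrast between a 3-day and a 10-day stay rests wholly on assumed exponential onset with medians of 7 to 16 days, and it falls to about 1.3-fold for 5 against 7 days. It applies to the events not named at follow-up, and less, if at all, to reoperation and neurological deficits. This is an inexpensive improvement that should be made; it does not invalidate the registry.

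**What to change.** 1. State the primary complication indicators over a fixed window from surgery, for example 30 days, regardless of discharge, and say which CRF items supply them.
2. Record the date of each event and the date of discharge.
3. Name infection, meningitis, stroke and death explicitly in the follow-up part. If the full CRF already has these items, saying so in the protocol is enough.
4. Keep the until-discharge rate as a secondary indicator.
5. Report, by centre, the share of patients with documented contact through the whole window.

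The cost is a few fields, taken from charts already opened for the 12-month follow-up. The downsides are that events treated elsewhere may be missed, unevenly between centres, and that stated complication rates may be somewhat higher. A 30-day limit also leaves later events out: under model A with a median of 12 days, 0.5^(30/12) = 18% of events fall after day 30, so the follow-up items are needed as well as the window.
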